### Data management and quality control

To ensure data quality and procedural adherence of our statistical analysis approach, we will implement a detailed data management plan. Quality control will be applied to each phase of data handling to safeguard data collection and process reliability.

#### Birth cohort data

Case report form data, as defined and dictated by our study protocol, will be collected and managed using iDataFax, an electronic data capture application with extensive management features including a data query system to help ensure study credibility. The iDataFax system will generate regular reports that summarize and track routine data collection. These reports will help the investigative team monitor and maintain data completeness during follow-up and achieve high data capture performance by minimizing missed scheduled clinical assessments, preventing or reducing missing data, and maintaining high cohort retention rates over the three months of regular infant assessment at our three participating centers.

#### NIRS data

NIRS data will be downloaded daily and uploaded to a secure server within 24 h of monitoring completion. The data coordinating center will download and process all NIRS files on a weekly basis. During data processing, quality control reports will be generated to summarize the expected and actual duration of NIRS monitoring, percent of missing data, and identify when 30 min or more of consecutive data are missing. This approach will ensure proper data collection for future analysis for the entire duration of the monitoring period and confirm that NIRS machines are working properly. If one of our checks fails, we will notify the study nurses who will flag the machine, assess and correct the issue. If issues continue, we will notify the NIRS machine manufacturer, Medtronic, Inc. (Boulder, CO) for technical support. These steps will ensure consistency of data collection across our three study sites. In addition to individual NIRS monitoring checks, quarterly reports summarizing the total number of patients with NIRS monitoring, patient characteristics, and summary statistics for measurements collected during NIRS monitoring will be generated and reviewed by study investigators and biostatisticians.

### Primary outcome

All infants enrolled who receive RBC transfusion will have MES-rSO_2_ measured by NIRS as the primary study end-point [INVOS 5100C Cerebral/Somatic Oximeter (Covidien, Boulder, CO)], a Food and Drug Administration approved device for use on premature infants. NIRS noninvasively measures regional tissue saturation (rSO_2_) in real time because it calculates the difference between oxyhemoglobin (HbO_2_) and deoxyhemoglobin (HHb) expressed as: rSO_2_ = HbO_2_/HbO_2_ + HHb [47]. WE will obtain a baseline measurement by placing the NIRS probes on the infant at least 30 min prior to transfusion (triggered by the decision to transfuse made by the clinical team). Probes will remain in place to collect data for 48 h following transfusion completion. Two-probe site monitoring on mesenteric and renal beds will be used to evaluate differential tissue bed oxygenation. Adhesive sensor probes are vertically applied to left periumbilical area for mesenteric monitoring and horizontally to right flank for renal monitoring.

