## Background

Necrotizing enterocolitis (NEC) is the most common gastrointestinal emergency among premature infants [1, 2], occurring in approximately 11% of those born < 29 weeks’ gestation [3]. Case-fatality rates are as high as 50% for extremely low birth weight (ELBW) infants (≤ 1000 g at birth) who develop NEC [4]. Survivors are at risk for substantial long-term complications including neurodevelopmental delay, nutritional deficit and failure to thrive [3, 5]. Costs associated with NEC in the United States are estimated at $1 billion annually [2]. Transfusion-related necrotizing enterocolitis (TR-NEC) refers to an observed phenomenon that specifically describes a premature infant who develops NEC within 48 h after receiving a red blood cell (RBC) transfusion. Several reports have identified RBC transfusions as a significant and independent risk factor for NEC [6–14]; however, others have not found an association [15–21], but rather an association with degree of anemia prior to NEC development, which has led to considerable controversy [18].

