No current biomarkers reliably predict NEC, limiting efforts to prevent this disease. The range of symptoms are highly variable, from subtle signs such as feeding intolerance and abdominal distention, to complete cardiovascular collapse and shock. Because NEC can progress to extensive bowel necrosis within hours, therapies are often ineffective [22]. Multiple factors are related to NEC etiology including prematurity, enteral feeding, pro-inflammatory propensity of the immature intestine, and impaired mesenteric blood flow [23]. The majority of premature infants receive transfusions for anemia of prematurity, and RBC transfusions precede approximately 25–38% of NEC cases [7, 14, 24]. Transfusion of different storage aged RBCs to premature infants has not been shown to contribute to the risk of NEC [7, 24]. However, the chronological storage age of RBCs may not be an accurate gauge of donor RBC function and the storage lesion may be exacerbated by gamma irradiation [25], which is performed to prevent transfusion-associated graft-vs-host disease. Although the Age of Red Blood Cells in Premature Infants (ARIPI) trial investigated the effects of total storage duration of RBCs in preterm infants [26], the study did not investigate the effects of irradiation [27]. Currently, the “safe” duration of RBC storage following irradiation (post-irradiation storage time, pIST) is unclear. Given the multifactorial etiology of NEC, preventative efforts will be more successful if clinicians understand the underlying pathophysiologic mechanisms and modifiable risk factors influencing the disease.

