## Methods

All RBC transfusions given to infants during hospitalization will be studied. All RBC transfused units are stored in citrate-phosphate-dextrose-adenine (CPDA-1) preservative solution. pIST and storage days will be recorded for each RBC transfusion. All infants will be monitored with NIRS prior to, during and up to 48 h following each transfusion. Consistent with epidemiologic reports of transfusion-related NEC and prior studies at the 3 centers, we anticipate approximately 20 (10%) infants will develop NEC while on study. For our 2:1 case-controlled metabolomic analysis, we will prospectively analyze 40 infants who do not develop NEC and compare to 20 infants with NEC. Within this sub-cohort, we will compare alterations in metabolic pathways from saRBC unit (in vitro) and infant blood sample (in vivo). We will then examine a third sub-cohort of 120 infants without NEC within the NEC “window” (29–34 postmenstrual weeks’). These infants will also be monitored weekly for 24–48 h with mesenteric NIRS to evaluate the relationship between anemic (hemoglobin < 8 g/dL) and non-anemic infants. Reports suggest that this specific population of infants are more likely to experience paradoxical reductions in MES-rSO_2_ substantially increasing the risk for NEC when transfusions are given [10, 36]. Analysis will also include assessment of hemoglobin as a continuous variable.

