### Statistical methods

We will use a novel statistical approach [51] implemented by the *NIRStat* R package for analyzing the NIRS data. Specifically, the *NIRStat* method models the observed MES-rSO_2_ time series with a nonparametric smooth function via penalized regression splines [49, 50]. It then provides accurate and robust statistical measures for characterizing the important features in rSO_2_ series. We will use the mean area under the fitted spline curves (MAUC) measure generated from the *NIRStat* package to measure the MES-rSO_2_ levels at baseline and then at post-transfusion. The MAUC changes from baseline to post-transfusion will be used to quantify the changes in MES-rSO_2_ due to transfusion. Two sample t-tests will be used to compare the changes in MAUC between saRBCs +/− pIST. Multivariate linear regression models will also be applied to model the changes in AUC in terms of pIST status (with pIST and without pIST) and other potential confounding factors. The multivariate analysis will allow us to assess whether the changes in MES-rSO_2_ differs significantly between saRBCs with pIST and those without pIST, controlling for other confounding factors.

The incidence of NEC and death will be estimated by the cumulative incidence function appropriate for competing risks. Gray’s method (modified log-rank test) will be used to compare NEC cumulative incidence according to baseline clinical characteristics. Cause-specific hazard ratios will be calculated to measure the degree of association between baseline characteristics and NEC, and between baseline characteristics and death by fitting a stratified Cox proportional-hazards regression model for competing risks. The competing risks model will be implemented using SAS PHREG using robust sandwich covariance matrix estimates to account for within-mother correlation that may occur in outcomes of multiple-birth infants.

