## Discussion

There is an urgent need for a large, hypothesis-driven, prospective study to examine the effect of both RBC unit and recipient factors on the physiologic perturbations that cause NEC [11]. Given that 75–90% of low birth weight infants receive one or more RBC transfusions [52, 53], it is reasonable to predict that NEC may result from a combination of pre-existing anemia and reduced intestinal oxygenation exacerbated by metabolic/functional changes in transfused RBCs, due to irradiation and pIST. This investigation may allow us to identify new modifiable factors that can be used to test targeted prevention strategies and mitigate this devastating disease.

We propose to investigate intestinal oxygenation changes that precede the development of NEC. Our overarching hypothesis is that irradiation of RBC units followed by longer storage times perturbs donor RBC metabolism and function, and these derangements are associated with paradoxical microvascular vasoconstriction, intestinal tissue hypoxia and injury and/or NEC in transfused premature infants with already impaired intestinal oxygenation due to significant anemia. Specifically, our primary goal is to characterize the association between metabolic changes in transfused RBCs relative to pIST, and adverse effects in the recipient by in vivo NIRS trend monitoring of intestinal oxygenation, and in vitro RBC functional studies. Our primary endpoint is changes in MES-rSO_2_ trends in response to transfusion of saRBC+/-pIST as measured by NIRS. The secondary endpoints are to determine the hazard ratio of NEC for low birth weight infants transfused with saRBCs +/-pIST, examine metabolomic fingerprints of transfused RBC in vitro, and examine the impact of anemia severity on MES-rSO_2_ trends.

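### NIRS is collected for 48 h after transfusion with no stated cut at NEC onset, so analyses linking MES-rSO2 to NEC may include readings taken after transfusion-related NEC has begun

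*Protocol article*

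**What the plan says.** Four parts of the protocol article bear on this.

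- **Collection window.** Methods: "All infants will be monitored with NIRS prior to, during and up to 48 h following each transfusion". Primary outcome: "Probes will remain in place to collect data for 48 h following transfusion completion".
- **Transfusion-related NEC.** The Background uses the term for a premature infant who "develops NEC within 48 h after receiving a red blood cell (RBC) transfusion".
- **Summary measure.** Under Statistical methods, MAUC from the fitted spline is used "to measure the MES-rSO_2_ levels at baseline and then at post-transfusion". The same section continues: "The MAUC changes from baseline to post-transfusion will be used to quantify the changes in MES-rSO_2_ due to transfusion". No separate averaging window is given, and nothing is said about readings after NEC onset. The NIRS data section describes quality checks meant to "ensure proper data collection for future analysis for the entire duration of the monitoring period".
- **Temporal aim and NEC-linked analyses.** The Discussion says: "We propose to investigate intestinal oxygenation changes that precede the development of NEC". Study design names the same gap. Secondary outcomes and the metabolomics part of the statistical text relate features of the transfused units to MES-rSO2 changes and to NEC. One planned contrast sets infants who have both a paradoxical saturation response and NEC against unaffected infants.

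**The concern.** The two 48 h periods coincide. An infant with transfusion-related NEC has, by the article's own description, an onset inside the period in which the post-transfusion signal is recorded. If that signal is summarised by one MAUC over the recorded period, part of it comes from bowel that is already diseased. The article itself notes that NEC can advance to extensive necrosis in hours, so a marked change in mesenteric saturation after onset is plausible.

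What is at stake is the direction of the oxygenation–NEC link. A low post-transfusion MAUC in a case could be a consequence of NEC and still be read as its forerunner. The contrast involving paradoxical responders is the most exposed, because a fall produced by NEC could itself place an infant in that group. The proposed mechanism would then seem confirmed by reverse causation.

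**Working it through.** **1. The plan's own figure.** Table 1 gives power 0.82 for a difference of 10, SD 18 and 110 transfused infants (55 per group). With two-sided alpha 0.05 (assumed, not stated), the noncentrality is 10 / (18 × √(2/55)) = 2.91. Power is 0.823 by the two-sample t-test and 0.830 by the normal approximation. All 20 filled cells of Table 1 reproduce to within 2 percentage points. The sample size arithmetic is not in dispute; the point concerns timing.

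**2. Number of cases concerned.** Methods expects about 20 NEC cases. The Background says "RBC transfusions precede approximately 25–38% of NEC cases", without a time limit. Reading that share as NEC within 48 h (an assumption):
- 20 × 0.25 = 5.0
- 20 × 0.38 = 7.6

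That is about 5 to 8 infants. The other 12 to 15 cases would have onset outside the window and are unaffected.

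**3. Share of a 48 h mean that lies after onset.** For onset at hour t the share is (48 − t)/48:

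| Onset (h) | Share after onset |
|---|---|
| 6 | 87.5% |
| 12 | 75% |
| 24 | 50% |
| 36 | 25% |

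**4. Shift in one affected infant.** Shift = fall after onset × share after onset. The article gives neither the size of the fall nor the onset hour. Assuming a sustained fall of 10 to 20 points and onset at 24 h:
- 10 × 0.5 = 5 points
- 20 × 0.5 = 10 points

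**5. Spurious NEC versus no-NEC difference.** Shift in the mean of the NEC group = share of cases affected × shift per affected infant:
- 0.25 × 5 = 1.25, about 1.3 points
- 0.38 × 10 = 3.8 points

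This arises with no change in saturation before onset. It assumes that all 20 cases contribute a post-transfusion MAUC. If never-transfused cases drop out, the affected share and the difference are larger.

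**6. Effect on the primary pIST comparison.** Let k be the number of affected infants, s the shift in each, and 55 the group size, with one analysed transfusion per infant. If the cases split 60/40 between the pIST groups, the difference moves by (0.6 − 0.4) × k × s / 55. If all fall in one group, it moves by k × s / 55. Here the assumptions are widened to a fall of 10 to 30 points and onset from 6 to 36 h, so s runs from 10 × 0.25 = 2.5 to 30 × 0.875 = 26.25:
- 60/40 split: 0.2 × 5 × 2.5 / 55 = 0.05 to 0.2 × 7.6 × 26.25 / 55 = 0.7 points
- all in one group: 5 × 2.5 / 55 = 0.2 to 7.6 × 26.25 / 55 = 3.6 points

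The design difference is 10 points.

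**The case against.** The strongest reply is that the article never says MAUC is averaged over 48 h. It says how long probes stay on, and in Methods only up to 48 h. The wording about the full monitoring period belongs to quality control of data capture. An analysis plan that is not shown could set a shorter window or stop at onset. This stands as a limit: the point rests on the plain reading of a collection period, a single post-transfusion MAUC, and a change attributed wholly to transfusion, with no cut stated.

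A reader might also infer more than the documents support:

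- **That the NEC hazard models are reverse-causal.** They are not: the competing-risks models use baseline characteristics, not MAUC. The anemia sub-cohort consists of infants without NEC. Metabolites of the transfused units are fixed before transfusion, so NEC cannot alter them. What remains exposed is the saturation side of the NEC-linked analyses, above all the paradoxical-response group. How that group is classified is not given.
- **That the primary comparison is compromised.** It is not, at the sizes in step 6. Moreover, NEC after transfusion may be a downstream effect of the exposure, so a total-effect MAUC by pIST can legitimately include it.
- **That the bias is as large as the effect the study is sized for.** The 5 to 10 points are shifts within one infant, whereas Table 1's 6 to 12 points are differences between pIST group means. The group-level figure of 1.3 to 3.8 is below the smallest tabulated difference and small against an SD of 9 to 18.
- **That the primary MAUC should be cut at onset.** Doing so would condition the primary endpoint on a post-exposure outcome and give cases shorter windows than non-cases, which can itself create a difference.

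**Conclusion.** The point holds for analyses that relate MES-rSO2 response to NEC, and not for the primary endpoint. As written, nothing keeps post-onset readings out of those analyses, and this undercuts the stated aim of studying changes that come before NEC. About 5 to 8 of 20 cases are concerned, with a spurious NEC versus no-NEC difference of about 1.3 to 3.8 points. The primary pIST contrast moves by about 0.05 to 0.7 points with a 60/40 split of cases, and by at most about 3.6 under extreme assumptions.

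These sizes depend on three assumptions the article does not supply: that 25–38% is the 48 h share, the fall after onset, and the onset hour. The overlap of the two 48 h periods does not depend on them. The change is worth making because it is cheap and removes an avoidable ambiguity about which came first.

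**What to change.** Leave the primary MAUC comparison by pIST unchanged. In Secondary outcomes and Statistical methods (including the metabolomics text), add that:

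- every analysis relating MES-rSO2 to NEC, including the classification of paradoxical responders, uses only NIRS recorded before the first recorded sign of NEC;
- the matched or comparison infants are given the same post-transfusion window length as the case, so that the cut does not itself produce a difference;
- the full-window MAUC is reported as a sensitivity analysis.

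The cost is a sentence or two of text, shorter and noisier windows in a handful of cases and their comparators, and NEC onset recorded by clock time and not only by date.

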### Secondary outcomes

We will examine the association between metabolic features of transfused RBC units and pre-transfusion pIST, alterations in MES-rSO_2_, and the development of NEC. Our analysis will include methods previously used [25, 48]. Our preliminary data examining distinct effects of gamma irradiation on saRBC identified four metabolite pathways that were significantly altered by storage (> 7 days) and irradiation: arachidonic acid, linoleic acid, steroid biosynthesis, and alpha-linoleic acid. Alterations in these pathways may worsen RBC function, and we propose this may be involved with adverse intestinal oxygenation following RBC transfusion that, in some infants, could lead to NEC. However, we will not pre-select pathways for the current analysis. Therefore, we will pursue analytic approaches previously described [25] to identify metabolites that discriminate those infants with paradoxical MES-rSO_2_ responses with NEC to unaffected infants, and we will also conduct an additional secondary analyses focused on biochemical pathways previously identified in storage saRBCs generated from metabolomics analyses.

### Statistical methods

We will use a novel statistical approach [51] implemented by the *NIRStat* R package for analyzing the NIRS data. Specifically, the *NIRStat* method models the observed MES-rSO_2_ time series with a nonparametric smooth function via penalized regression splines [49, 50]. It then provides accurate and robust statistical measures for characterizing the important features in rSO_2_ series. We will use the mean area under the fitted spline curves (MAUC) measure generated from the *NIRStat* package to measure the MES-rSO_2_ levels at baseline and then at post-transfusion. The MAUC changes from baseline to post-transfusion will be used to quantify the changes in MES-rSO_2_ due to transfusion. Two sample t-tests will be used to compare the changes in MAUC between saRBCs +/− pIST. Multivariate linear regression models will also be applied to model the changes in AUC in terms of pIST status (with pIST and without pIST) and other potential confounding factors. The multivariate analysis will allow us to assess whether the changes in MES-rSO_2_ differs significantly between saRBCs with pIST and those without pIST, controlling for other confounding factors.

The incidence of NEC and death will be estimated by the cumulative incidence function appropriate for competing risks. Gray’s method (modified log-rank test) will be used to compare NEC cumulative incidence according to baseline clinical characteristics. Cause-specific hazard ratios will be calculated to measure the degree of association between baseline characteristics and NEC, and between baseline characteristics and death by fitting a stratified Cox proportional-hazards regression model for competing risks. The competing risks model will be implemented using SAS PHREG using robust sandwich covariance matrix estimates to account for within-mother correlation that may occur in outcomes of multiple-birth infants.

To guard against model overfitting, we will employ both clinical and statistical criteria in making decisions about which independent variables to include; and we will limit the number of candidate variables. In general, the results of models having fewer than 10 outcome events per independent variable are thought to have questionable accuracy and the tests of statistical significance may be invalid. The use of “machine-learning” covariate selection methods, such as bootstrap bagging, will be utilized to improve the reliability of identifying risk factors for NEC and death. The hazard ratio and its 95% confidence interval (CI) will be calculated for each factor in the presence of others in the final model for NEC and mortality.

For metabolomics analysis, we will examine associations between metabolic features of transfused RBC units and pre-transfusion pIST, alterations in MES-rSO_2_, and the development of NEC using an approach previously described [25]. Correlative analyses without pre-selecting specific metabolic pathways will be performed. Methods of analysis will include a number of gene set analysis, such as MSEA and MetaboAnalyst. We can also borrow from the gene expression packages to conduct more complex analysis of metabolite-set differential expression analysis as well as metabolite-set differential coordination analyses. The pathway level analysis will be followed by the detection of metabolites that contribute the most to the changes of metabolic pattern using the built-in scoring system of the packages.

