##### Sample size estimation

We aim to enroll a total of 220 infants into the study. We assume 110 of these infants (50%) will receive RBC transfusion and undergo NIRS monitoring. Analysis comparing two groups, divided equally among infants by pIST, would provide more than 80% power to detect a difference of 10% in pre- and post-transfusion mean area under the curve MES-rSO_2_ change (standard deviation = 18) between groups or 90% power to detect a difference as small as 6% in MES-rSO_2_ with a standard deviation of 9 (Fig. 1 and Table 1). However, the number of infants enrolled in the study that receive a transfusion and have NIRS monitoring may be lower than 110. Therefore, we have provided power estimates for analysis of a sample size of 72 infants with RBC transfusion and NIRS monitoring (33% of the enrolled cohort). This will generate 80% power to detect a difference of 12% in pre- and post-transfusion mean area under the curve MES-rSO_2_ change between the two groups if the final sample size is 72 infants (36 per group) and the estimated standard deviation for MES-rSO_2_ change is 18. A secondary analysis evaluating pIST a continuous variable will also be performed, which will likely yield greater power for each of the scenarios presented.

**Table 1 Tab1:** Sample Size and Power Estimates

Groups	*n* = 220 transfused				*n* = 110 transfused				*n* = 72 transfused			
	SD = 9		SD = 18		SD = 9		SD = 18		SD = 9		SD = 18	
Difference in MES-rSO_2_ AUC change (%)	Effect Size	Power	Effect Size	Power	Effect Size	Power	Effect Size	Power	Effect Size	Power	Effect Size	Power
6	0.67	1	0.33	0.69	0.67	0.93	0.33	0.41				
8	0.89	1	0.44	0.91	0.89	1	0.44	0.64				
10	1.11	1	0.56	0.98	1.11	1	0.56	0.82	1.11	1	0.56	0.64
12	1.33	1	0.67	1	1.33	1	0.67	0.93	1.33	1	0.67	0.8

Abbreviations: *MES-rSO*_*2*_ mesenteric regional oxygen saturation, *AUC* area under curve, *SD* standard deviation

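### The primary analysis does not fix its unit: power counts infants, pIST and MES-rSO2 response are recorded per transfusion, and the named tests make no allowance for correlation within infant or mother

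*Protocol article*

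**What the plan says.** Three sections of the protocol article bear on the unit of the primary analysis.

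- **Methods** sets data collection at transfusion level: "All RBC transfusions given to infants during hospitalization will be studied", "pIST and storage days will be recorded for each RBC transfusion", and "All infants will be monitored with NIRS prior to, during and up to 48 h following each transfusion".
- **Sample size estimation** works at infant level: "We assume 110 of these infants (50%) will receive RBC transfusion and undergo NIRS monitoring", with the comparison described as "Analysis comparing two groups, divided equally among infants by pIST". The fallback is 72 infants, 36 per group.
- **Statistical methods** words the comparison by blood product: "Two sample t-tests will be used to compare the changes in MAUC between saRBCs" with and without pIST, and then "Multivariate linear regression models will also be applied to model the changes in AUC in terms of pIST status" and confounders. It names no random effect, GEE, cluster-robust variance or rule for choosing one transfusion per infant.

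The one provision for correlated data is in the competing-risks Cox model for NEC and death, which uses "robust sandwich covariance matrix estimates to account for within-mother correlation that may occur in outcomes of multiple-birth infants".

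**The concern.** pIST belongs to the transfused unit, so an infant transfused more than once may receive units of both types. The Background describes infants of this birth weight as often transfused, so repeats are to be expected. The three sections then do not describe one analysis:

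- If every monitored transfusion enters the t-test or regression, observations from one infant, and from siblings, are correlated. Both named methods assume that they are not.
- If one value per infant enters, nothing says which transfusion supplies it or where an infant with both unit types belongs. Siblings are still correlated.

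At stake are the p-value and confidence interval of the primary endpoint. Choosing between the two readings after the data are seen would also leave analytic freedom where there should be none.

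**Working it through.** **Step 1. Reproduce Table 1.** Inputs from Sample size estimation: 110 infants (55 per group) or 72 (36 per group), SD 9 or 18, differences 6 to 12. Alpha is not stated; two-sided 0.05 is assumed. With effect size d = difference/SD and a two-sample noncentral t with one observation per infant:

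| Infants | Difference | SD | d | Stated power | Recomputed |
|---|---|---|---|---|---|
| 110 | 10 | 18 | 0.56 | 0.82 | 0.823 |
| 110 | 6 | 9 | 0.67 | 0.93 | 0.934 |
| 110 | 6 | 18 | 0.33 | 0.41 | 0.410 |
| 72 | 12 | 18 | 0.67 | 0.80 | 0.797 |
| 72 | 10 | 18 | 0.56 | 0.64 | 0.642 |

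All 20 filled cells agree (one saturated cell was checked by normal approximation only). Table 1 is thus a calculation with one independent value per infant.

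**Step 2. Pool all transfusions in an unadjusted t-test.** The article gives neither transfusions per infant (m) nor the within-infant correlation of MAUC change (ICC), so both are assumed. Simulation under no pIST effect used 110 infants, a random infant intercept and 4,000 runs per scenario (Monte Carlo standard error at 5%: √(0.05 × 0.95/4000) = 0.0034). Selected scenarios, type I error at nominal 0.05:

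| m | ICC | pIST constant within infant | Partly clustered | Independent of infant | Alternating within infant |
|---|---|---|---|---|---|
| 2 | 0.1 | 0.057 | 0.056 | 0.055 | 0.040 |
| 2 | 0.5 | 0.104 | 0.069 | 0.051 | 0.009 |
| 3 | 0.3 | 0.113 | 0.079 | 0.057 | 0.018 |
| 4 | 0.5 | 0.220 | 0.114 | 0.049 | 0.006 |
| mean 3, varying | 0.2 | 0.111 | 0.071 | 0.047 | not run |
| mean 3, varying | 0.4 | 0.174 | 0.092 | 0.050 | not run |
| mean 5, varying | 0.2 | 0.163 | 0.092 | 0.048 | not run |
| mean 5, varying | 0.4 | 0.247 | 0.126 | 0.055 | not run |

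In the partly clustered column, rows with fixed m give each infant a uniform(0,1) probability of a long-pIST unit; rows with varying m use a latent within-infant exposure correlation of 0.5.

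Check on the constant case: the design effect is 1 + (m − 1) × ICC, which for m = 4 and ICC 0.5 is 2.5. Type I error is then about 2Φ(−1.96/√2.5) = 2Φ(−1.24) ≈ 0.215, against 0.220 simulated.

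**Step 3. Use one value per infant.** With 50/50 exposure and independent units, the share of infants with both types is 1 − 2(0.5^m): 50% for m = 2 and 75% for m = 3. If each infant has a uniform probability of a long-pIST unit, as in Step 2, the share is 1 − 2/(m + 1): 33%, 50% and 60% for m = 2, 3 and 4. If pIST is constant within infant it is zero.

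**Step 4. Power if repeats are modelled.** With pIST constant within infant, which is the least favourable case, the effective number per group is 55m/[1 + (m − 1) × ICC]. For difference 10 and SD 18:

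- m = 2, ICC 0.5: 110/1.5 = 73.3, power 0.916.
- m = 3, ICC 0.3: 165/1.6 = 103.1, power 0.978.

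Over m = 2 to 4 and ICC 0.1 to 0.5 the range is 0.916 to 0.999, above the stated 0.82. This takes SD 18 as the SD of a single transfusion's change.

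**The case against.** The strongest reply is that no sentence says each transfusion enters the primary test as an independent observation. Studying every transfusion may describe data collection only, and the sample size section points to one value per infant. This is also a condensed article, and the handling of repeat transfusions may sit in a fuller plan. This reply stands in part: a reader might infer that the article declares transfusions independent, and it does not. It does, however, name the primary test, describe the groups by infant in one place and by blood product in another, and deal with clustering for a secondary endpoint alone. That mismatch is on the page and is more than silence.

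A reader might also infer that the stated power is wrong. The documents do not support that. Table 1 reproduces and stands for one independent value per infant, and repeats from the same infants, properly modelled, would raise power. Power would fall below Table 1 if the 110 were transfusions (0.785 to 0.437 for difference 10, SD 18, over the Step 4 range), but the article says they are infants.

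The direction of error is also open. The largest inflation needs pIST constant within infant, when no infant has mixed exposure. The 50% and 75% mixed shares need pIST independent of infant, when pooling is about nominal. These extremes cannot both apply. With partial clustering, both problems occur in milder form.

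**Conclusion.** The concern holds as a failure to fix the unit of the primary analysis, together with named tests that do not fit the data structure on either reading.

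- **All transfusions pooled:** type I error at nominal 5% is about 6–13% with partial clustering of pIST within infant, about 6–25% if pIST is constant, about 5% if it is independent of infant, and about 0.6–4% if it alternates within infant. These figures rest on assumed ICCs of 0.1 to 0.5, 2 to 5 transfusions per infant, 110 infants and two-sided 5%. The article gives no basis for choosing among the scenarios.
- **One value per infant:** Table 1 stands apart from sibling correlation, whose size cannot be judged because the share of multiples is not given. Infants with both unit types have no defined group.

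The p-value and confidence interval for the primary endpoint cannot be interpreted until one reading is chosen.

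**What to change.** State the unit of the primary analysis in Statistical methods, by one of two routes, before outcome data are examined.

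1. **All transfusions (preferred, as it uses everything collected).** Replace the t-test and ordinary regression with a transfusion-level linear mixed model for the baseline-to-post-transfusion MAUC change on pIST and the chosen confounders, with random intercepts for infant within mother. GEE or a robust variance clustered on mother is an alternative. Say in Sample size estimation that Table 1 applies to one independent value per infant, and add power for the clustered model over a range of ICC and transfusions per infant.
2. **One index transfusion per infant.** Prespecify the rule that selects it, group the infant by that unit's pIST, keep Table 1, and use a mother-clustered variance.

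The outcome (MAUC change) and the 48 h monitoring period stay as they are under both routes. The cost is a few sentences in Statistical methods and, for the first route, an added power paragraph. No new data are needed.
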